### Data collection and measures

The qualitative interviews will follow partly structured interview guides developed according to theory on quality of life, meaningful activity, motivation and earlier research on experiences of being overweight and obese. The interviews will be recorded, transcribed and analysed as text.

In the RCT, at baseline (T0), key aspects of overweight in adolescence will be assessed in relation to physical activity and quality of life (HRQOL). The effectiveness of the individual intervention will be addressed by assessing the key aspects before the intervention (baseline), directly after the intervention (6 months) (T1) and at one follow-up measure (T2). Thus, all the included adolescents complete questionnaires and tests on physical activity, fitness, diet, quality of life, self-efficacy, BMI, exercise motivation and socio-demographic variables. Physical activity will be measured with the relevant part of the Young-HUNT questionnaire (HUNT, 2006), validated for use in adolescences (ages 13 to 18 years) (Rangul et al., 2006). Fitness will be tested with a maximal multistage 20 m shuttle run test (Leger et al., 1988). The adolescents’ diet will be considered using a pre-coded food diary, validated for use in a Norwegian adolescent population (Andersen et al 2005). Health related quality of life will be measured with the Norwegian version of Kidscreen (Haraldstad et al 2010), and self efficacy with the widely used 8-item version of Schwarzer’s self-efficacy scale (Schwarzer 1993). Exercise motivation will be measured by the Exercise Regulations Questionnaire (BREQ-2) which will be

translated to Norwegian and validated as part of the study (Markland & Tobin 2004). In addition to the measures at T0, T1 and T2, the adolescents will perform structured activity registrations, write narratives on the blog, and a smaller sample will be interviewed.

### **Sample**

Based on power calculation the sample size in the RCT will be 100 (intervention group) + 100 (control group). The sample size (N) is dependent upon the planned statistical analysis. In this study several complicated analysis will be performed and it is not easy to estimate N without doing a proper power-analysis where all the necessary factors are taken into consideration. This will be done before setting the final sample-size. At this point we give a rough estimate of the needed sample size (Hinkle et al 2003). Given an effect size of 0.5, a significance level at 0.01, power at 0.80 and a two-tailed significance test we estimate N to be 96 in each group ([http://hedwig.mgh.harvard.edu/sample\\_size/quan\\_measur/para\\_quant.html](http://hedwig.mgh.harvard.edu/sample_size/quan_measur/para_quant.html)). At this point we consider a sample size at 100 (intervention group) + 100 (control group) to be sufficient.

The adolescents eligible for selection to the qualitative study will be approximately 100 (the intervention group). In a qualitative study the sampling plan is evaluated in terms of adequacy and appropriateness (Polit and Beck 2004) Adequacy refers to the sufficiency and quality of data the sample yields and appropriateness concerns the methods used to select the sample. A strategic sampling, within the intervention group, aimed at maximum variation according to gender, ethnicity and socio-demographic variables seem to be an appropriate sampling procedure here. Thus the sample will consist of overweight and obese adolescents of both genders taking part in an intervention. Sampling continues until saturation is achieved (Polit and Beck 2004), which means when an informational adequacy has been reached. A roughly estimated sample size would be 20-30 adolescents in the qualitative study.

### **Analysis**

The differences between the intervention and control group will be performed using repeated measure analyses for each of the dependent variables in a mixed effect model in SPSS 16. This approach is flexible and it is possible to model the dependence between observations from the same individual. There may also be class and school effects and these can similarly be accounted for. (Fitzmaurice et al 2008). Growth-curve analyses will also be considered given the three different points of measurement.

The structured blogs will be analyzed using descriptive statistics and testing differences in frequency, intensity and duration of the physical activity between the intervention group and the control group (Polit and Beck 2004).

The blog narratives and the qualitative interviews will be analyzed according to Kvale and Brinkmann (2009), implying a hermeneutic approach to data collection and analysis. Hermeneutics is the study of the interpretation of texts and the purpose is to obtain valid understanding and meaning of the texts. Following the guidelines of Kvale and Brinkmann (2009), the analysis will be done within three different contexts: self-understanding, critical common sense, and theory. In the first context, the transcribed interviews will be read and summarized. All interviews will then be re-read and coded, after which categories are assigned using descriptive terminology. The next step will be to interpret the findings by asking questions about meaning within the frame of critical common sense. During the interpretation process, patterns emerge that form the basis for the presentation of the results. In the third context, the findings will be interpreted and discussed in light of the study framework and earlier research.

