### **Design, sample and an overview of the study**

The design of the study is a complex intervention study with a multi-method design, consisting of a randomized controlled trial and a qualitative study. The sample will be drawn from schools in Oslo. Oslo will be divided into four sectors to secure variation on socio-demographic variables. Overweight adolescents will be randomly selected within each sector and placed in the intervention group or control group respectively. The sampling will be based on objective measures of weight and height and using Cole’s index to define overweight and obesity. Weight and height will be measured by the school nurse and will be coordinated with her regular meetings with the adolescents in 7th grade. New guidelines for weight control will be implemented in Norwegian schools, most likely during 2010. This means all pupils in the 7th grade will have their weight and height measured by the school nurse. The study group will receive the web-based intervention and the control group will receive standard care. At baseline, 6 months and 1 year both the experimental group and the control group will be measured at relevant variables. In the qualitative part of the study, in depth interviews with the adolescents in the intervention group will be performed and they will write daily unstructured blogs on the web. The sampling procedure for the qualitative part of the study will follow the sampling procedure of the intervention study. From the intervention group, a strategic or purposive sample of adolescents will be asked to participate in the qualitative part (Gerrish and Lacey 2006). A sample of maximum variation according to gender and socio-demographic variables is intended. Sampling continues until saturation is reached and the adolescents will be interviewed in depth before the intervention starts, further at 6 and 12 months after the intervention is ended.

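### Sector shapes selection and placement but is not named in the analysis; fitting it is a free, small gain in precision for comparisons of arm levels

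*Protocol*

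**What the plan says.** In its section on design, sample and overview, the protocol creates the sectors for a stated purpose: "Oslo will be divided into four sectors to secure variation on socio-demographic variables". It then says: "Overweight adolescents will be randomly selected within each sector and placed in the intervention group or control group respectively". The natural reading is that both selection and placement happen within sector. The section does not describe the method of allocation, any blocking, or numbers per arm within a sector. It gives three measurement times: "At baseline, 6 months and 1 year both the experimental group and the control group will be measured at relevant variables".

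The Analysis section plans "repeated measure analyses for each of the dependent variables in a mixed effect model in SPSS 16". It adds that "it is possible to model the dependence between observations from the same individual" and, on grouping, that "There may also be class and school effects and these can similarly be accounted for". The wording on class and school is permissive, and sector is not mentioned. A second paragraph plans between-arm tests of the frequency, intensity and duration of physical activity from the structured blogs. No grouping term is stated for those tests.

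The Sample section sets 100 per arm, from an effect size of 0.5, a two-sided level of 0.01 and power of 0.80.

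**The concern.** Sector is the one grouping that the design itself creates. It was chosen for socio-demographic spread, and the Target group section says that overweight is more common in some parts of Oslo, so outcomes may differ between sectors.

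If they do, an arm comparison without sector leaves the between-sector variance in the error term. The consequence depends on how pupils were placed:

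- **Arms balanced within sector.** The design has already removed sector differences from the arm contrast, but the reported standard error still includes them. It is too large and the test is somewhat conservative.
- **Arms not balanced within sector.** The standard error is honest, but the estimate is noisier than it need be.

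In both cases precision is at stake, not false positives. The optional class and school terms cannot be relied on to recover it, because the protocol does not commit to them.

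**Working it through.** **Inputs.** From the protocol: four sectors; 100 + 100 adolescents; d = 0.5; two-sided alpha 0.01; power 0.80; three measurement times. Assumed, because the protocol gives no figure: the share r of outcome variance between sectors (1% to 10%), a school share of 5%, 16 or 40 schools, each school lying in one sector.

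**1. The plan's own figure.** The two-sample t-test solution for d = 0.5, alpha 0.01 and power 0.80 is 95.1, so 96 per group, as stated (94 by the normal approximation). At 100 per group, power by the normal approximation is 0.831. The point does not touch this calculation.

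**2. Sector alone, level comparison at one time.** With total SD 1, the standard error is √(2/100) = 0.1414 without sector and √(2(1 − r)/100) with it. The ratio is 1/√(1 − r). If arms are balanced within sector, the actual level of the 0.01 test without sector is 2(1 − Φ(2.576/√(1 − r))).

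| r | SE ratio | Power at SD 1 → SD √(1 − r) | Actual level if balanced, sector omitted |
|---|---|---|---|
| 0.01 | 1.005 | 0.831 → 0.836 | 0.0096 |
| 0.02 | 1.010 | 0.831 → 0.840 | 0.0093 |
| 0.05 | 1.026 | 0.831 → 0.854 | 0.0082 |
| 0.10 | 1.054 | 0.831 → 0.875 | 0.0066 |

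Simulation with exactly 25 per arm per sector gives power without and with sector of 0.829 and 0.846 at r = 0.05, and 0.838 and 0.872 at r = 0.10.

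**3. Without balance by sector.** With 100:100 randomisation that ignores sector, the simulated level without sector in the model is 0.0102 at r = 0.05 and 0.0102 at r = 0.10, which is nominal. Fitting sector still reduces residual variance by the share r. Chance imbalance now costs something: three extra terms inflate the variance by about 198/195 = 1.015, or 0.8% of the standard error. There is thus a net gain only when r exceeds about 1.5%.

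**4. With school in the picture (pupils allocated individually, balanced by sector, school share 5%).** Model-based standard errors of the arm difference at one time:

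| Schools | r | Neither | School only | School + sector | Neither / both | School only / both |
|---|---|---|---|---|---|---|
| 16 | 0.02 | 0.1414 | 0.1383 | 0.1380 | 1.025 | 1.002 |
| 16 | 0.05 | 0.1414 | 0.1368 | 0.1360 | 1.040 | 1.006 |
| 16 | 0.10 | 0.1414 | 0.1330 | 0.1320 | 1.071 | 1.008 |
| 40 | 0.02 | 0.1414 | 0.1401 | 0.1392 | 1.016 | 1.006 |
| 40 | 0.05 | 0.1414 | 0.1388 | 0.1369 | 1.033 | 1.014 |
| 40 | 0.10 | 0.1414 | 0.1362 | 0.1331 | 1.063 | 1.023 |

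A fitted school effect absorbs most of the sector variance, leaving an excess of 0.2% to 2.3%. The larger figures in the *neither* comparison include the benefit of fitting school as well as sector.

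**5. Arm-by-time change contrast.** The standard error is the same with and without sector: 0.1220, 0.1200 and 0.1166 at r = 0.02, 0.05 and 0.10. A sector difference that is constant over time cancels within the person.

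**The case against.** The strongest case against has five parts.

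- **No closed model.** The Analysis section calls the approach flexible and excludes nothing. A full covariate list is commonly left to the statistical analysis plan, which is not at hand. This stands, and is why the point is an improvement and not an error. Still, the section does discuss grouping levels and leaves out the one that the design uses.
- **Balance is not stated.** A reader might infer that the real type I error falls below 0.01. The documents do not support this: it follows only if arms are balanced within sector, and step 3 shows a nominal level otherwise.
- **Repeated measures.** A reader might infer that confidence intervals are too wide for every outcome. They are not for change contrasts, a natural test with three time points. But the protocol does not fix the contrast, and for the blog tests no repeated-measures, baseline or school term is stated, so cancellation cannot be assumed there.
- **School covers it.** Largely true if school is fitted and pupils are allocated individually, but school is optional. If whole schools were allocated, which the protocol does not say, the picture changes: omitting sector from a model with school makes the standard error about 4% to 36% too large, while omitting both makes it about 5% to 20% too small.
- **The size is assumed.** This stands. Differing prevalence of overweight across Oslo does not show that outcomes differ by sector among adolescents already selected as overweight. Power at 100 per arm is also above 0.80 without sector in these calculations.

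**Conclusion.** The omission is real: adolescents are selected and, on the natural reading, placed within sector, and the analysis does not name it. The consequence is conditional and small. For comparisons of arm levels at a time point and for the blog activity tests, leaving out both sector and school gives up some precision. With balance within sector, reported standard errors are about 0.5% to 5% too large at an assumed sector share of 1% to 10%. With school fitted and pupils allocated individually, the excess is about 0.2% to 2.3% (sector share 2% to 10%, school share 5%). Change contrasts are unaffected by constant sector differences. It is not established that the trial's standard errors are too large in general, or that its type I error differs from 0.01. Minor severity: a free improvement.

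**What to change.** In the Analysis section, state that arm comparisons, including the between-arm tests of blog activity, include sector (four levels, three indicator terms) as a fixed effect, alongside the random effect for the adolescent and any class or school terms. In the design section, state whether allocation is stratified by sector.

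The cost is a sentence in each place and three degrees of freedom out of about 200 participants. No new data are needed, because sampling is by sector. If allocation proves not to be balanced by sector and sector explains very little variance (below about 1.5%), the adjustment roughly breaks even or loses less than 1% of the standard error.

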#### *The study.*

The intervention will consist of three meetings between the adolescent, the parents and the researchers, and weekly web-based blog-counselling. The intervention period is six months and during the intervention and the follow up period the adolescents will be interviewed three times.

Three Meetings. At the 1st meeting the adolescents will fill in the baseline data and the adolescents that consent to take part in the qualitative study will participate in the first interview. The first meeting will also be an introductory meeting where the adolescent and his/her parents will be informed thoroughly about the purpose of the study as a whole and especially about the intervention. It will be made clear that the goal of the intervention is to increase physical activity, fitness and quality of life through meaningful activities. Weight reduction is not focused; however, it is desired to prevent weight gain through increased physical activity. The 2nd meeting will take place one week later and at this meeting the individual intervention is constructed together with the adolescent and the parents. An activity plan is made up according to the following criteria: The goal of the activities is to increase fitness and the activities should be perceived meaningful by the adolescents. Further the activity plan should be made up according to frequency of the activity (preferred daily); intensity of the activity (increased pulse, increased breath frequency); duration of the activity (1 hour a day); variation between purposeful activity (e.g. walking to school) and joyful activities (e.g. joining a dance class), and finally including some social activity. The second meeting should also prepare for the blog-counselling. The 3rd meeting will take place at the end of the intervention (after 6 months) and the purpose is to evaluate the intervention and motivate the adolescent to continue with physical activity. In addition the adolescent will fill in the questionnaires at this time and those participating in the qualitative study will be interviewed. The same instruments will be filled in at a follow-up after 1 year and the third qualitative

interview with the adolescents will take place. In addition qualitative interviews will be performed with the parents of the adolescents taking part in the qualitative study at the one year follow-up.

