Diaries and blog-counseling. A web-based, partly structured diary (blog), on activity and narratives about how their day has been is filled in by the adolescents daily. Personal blog-counseling is given once a week during the first three months, thereafter once a month during the next three months. The counselling will be given within in a frame of self-determination theory, the theory of self-efficacy and quality of life. The purpose of this counselling is to give individualised response to each adolescent and support and motivate them according to their needs.

| Overview of the intervention:                                                                                                                                                                                                                                                                                                                                                                                                                                                                                                                                                                                                                                                                                                                                                                                                                                                      | Overview of the qualitative part:                                                                                                                                                                                                                                                                                                                                                                                                                                                                                                                                                                  |

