| 
Meeting the adolescent and the parents 1:
 
 
• Base-line (T0)
 
• Introduction
 
 
Meeting the adolescent and the parents 2:
 
 
• Constructing an activity plan
 
• Introducing the blogs and the chat-room
 
• “Starting up”
 
 
Activity plan is carried out
 
 
• Blog-counselling and motivation for six months
 
 
Meeting the adolescent and the parents 3:
 
 
• Evaluating
 
• Filling in questionnaires (T1)
 
• In depth interview 2
 
 
Follow up after one year:
 
 
• Filling in questionnaires (T2)
 
• In depth interview 3
 
 | 
Meeting the adolescents 1:
 
 
• Qualitative in-depth interviews with adolescents (T0)
 
 
During the intervention period:
 
 
• Unstructured blog narratives
 
 
Meeting the adolescents 3:
 
 
• Qualitative in-depth interviews with adolescents (T1)
 
 
Follow up after one year:
 
 
• Qualitative in-depth interviews with adolescents and parents (T2)
 
 |

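### The Analysis section plans a between-arm test on structured-blog data, but the blog is described as part of the intervention and the protocol does not say whether controls keep one

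*Protocol*

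**What the plan says.** The Analysis section first plans a mixed-effects repeated-measures model for each dependent variable. It then turns to the blog data: "The structured blogs will be analyzed using descriptive statistics", and by "testing differences in frequency, intensity and duration of the physical activity between the intervention group and the control group". That one sentence fixes both the data source and the contrast.

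The design sections describe the blog as follows.

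- Design, sample and an overview of the study: "The study group will receive the web-based intervention and the control group will receive standard care". The measurement assigned to both groups is by visit: "At baseline, 6 months and 1 year both the experimental group and the control group will be measured at relevant variables".
- The study: "The intervention will consist of three meetings between the adolescent, the parents and the researchers, and weekly web-based blog-counselling". Of the visit one week after baseline it says: "The second meeting should also prepare for the blog-counselling".
- The study, paragraph on the daily diary: "A web-based, partly structured diary (blog), on activity and narratives about how their day has been is filled in by the adolescents daily". Counsellors respond individually, weekly for three months and then monthly for three.
- Overview table, intervention column, meeting 2: "Introducing the blogs and the chat-room", listed beside construction of the activity plan.

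One sentence under Data collection and measures is open. Having spoken of every included adolescent completing the T0, T1 and T2 instruments, it adds that the adolescents will also make structured registrations of activity and write on the blog. It does not say which arm is meant.

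**The concern.** A between-arm test needs the same variable, collected in the same way, in both arms. Here the instrument is also the channel through which the treatment is delivered. The plan therefore commits to a comparison without saying where the control observations come from or under what conditions they are recorded.

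Physical activity is one of the three domains named under Aim and hypothesis. A published blog comparison would look like randomised evidence on it. If the comparator is missing or measured differently, readers could mistake a product of the measurement for an effect of the programme. The question also has to be settled before the web system and control procedures are fixed, because a daily control diary cannot be collected afterwards.

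**Working it through.** **The plan's own figure.** The only related number is the sample size: effect size 0.5, two-sided alpha 0.01, power 0.80, giving 96 per group.

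- Normal approximation: n = 2 × ((2.576 + 0.842) / 0.5)² = 93.4, so 94 per group.
- Two-sample t-test: 95.1, so 96 per group, as stated.
- Power with 100 per group: 0.83 (normal) or 0.82 (t).

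The figure reproduces and is not in dispute. It says nothing about the blog comparison, which depends on who supplies blog data.

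**Does the blog belong to one arm?** Four places point that way: standard care for controls, blog-counselling in the definition of the intervention, preparation for it at the second intervention meeting, and the listing of the blog in the intervention overview. Two further places agree. The Design section ties the daily unstructured blogs to the intervention group. The Time Schedule has a partner relating diary blogs and counsellor responses to outcomes, which treats the blog as part of the intervention process. No sentence gives controls an account, a blog or an equivalent log. Against this stand the sentence under Data collection and measures that names no arm, and the Analysis sentence itself, which presupposes control data. Both readings therefore have to be followed through.

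**Reading A: controls keep no blog.** Up to 100 intervention adolescents contribute and 0 controls do. No between-arm test exists, whatever the sample size.

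**Reading B: controls also register activity on the blog.** Control data exist and the groups are still randomised, but three problems follow.

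1. Controls carry out daily web-based self-monitoring, which the protocol presents as part of the intervention. That departs from standard care. If self-monitoring changes behaviour, it reduces the contrast between arms for every outcome, not only for the blog variables.
2. The conditions of recording differ. On the stated schedule, an intervention adolescent receives about 13 weekly and 3 monthly responses (13 + 3 = 16 over six months, taking three months as 13 weeks). None is described for controls. Adolescents writing to a counsellor whose task is to motivate them may report more favourably and more completely than those writing to no one.
3. The blog starts at meeting 2, one week after baseline. The intervention arm has no blog measure from before the intervention against which to check or adjust reporting.

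**What is unaffected.** All included adolescents are assessed at T0, T1 and T2 with the Young-HUNT activity questions and the 20 m shuttle run. Both fall under the mixed model that the Analysis section plans first.

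**The case against.** The strongest reply is that the protocol nowhere says that controls lack a blog. Standard care describes treatment, not data collection. The registrations sentence follows directly on one about all included adolescents, and it lists structured registrations separately from blog narratives. On that view the Analysis sentence is coherent and only the control procedure is left undescribed. This much stands: a reader might infer that, as written, no control contributes data, but that is an inference from the design sections, not a statement in them.

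It also stands that under reading B the comparator is randomised, and that dilution by self-monitoring would pull towards no difference. A reader might want to express that dilution as a share of the planned effect. The documents do not support a figure: they give no self-monitoring effect, and the effect size of 0.5 is a rough planning value not tied to blog activity.

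Nor is Young-HUNT free of the problem. It is also self-reported, and the protocol describes no blinding of participants. It is stated to be validated for ages 13 to 18, while the ages of the 7th-grade sample are not given. Its advantage is narrower: both arms complete it at the same visits, and it is not the medium of counselling.

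The reply does not rescue the test. If controls do log activity, the conflict with standard care and the one-sided counsellor feedback remain.

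**Conclusion.** The planned between-arm blog test is unsound on either reading: it has no control data, or it compares entries gathered under different conditions while giving controls part of the intervention. This rests on the protocol text alone. The possible difference in reporting under reading B is a judgement about likely behaviour; its size is unknown.

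A reader might go further and conclude that the trial has no valid randomised comparison of physical activity. The protocol does not support that. The Young-HUNT measure and, for fitness, the shuttle run are taken in both arms and analysed in the main model, and nothing marks the blog comparison as primary. The point should be fixed, but the main comparison does not depend on it.

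**What to change.** Replace the Analysis sentence on structured blogs with text to this effect:

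> Structured blog data will be summarised descriptively within the intervention group only: adherence, amount of the programme received, and trajectory over the six months. The between-group comparison of physical activity will use the Young-HUNT measure at T0, T1 and T2 in the mixed model described above; fitness will be compared in the same way using the shuttle run.

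The text should not promise separate Young-HUNT results for frequency, intensity and duration unless the sponsor confirms that the questionnaire items provide them. The protocol refers only to the relevant part of the questionnaire.

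The registrations sentence under Data collection and measures should name the arm it applies to.

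If the sponsor does intend controls to keep an activity log, the Design, Data collection and Analysis sections must be reconciled to say so: what controls complete, whether anyone responds to it, and how this fits with standard care. The comparison should then be labelled supplementary and open to differential reporting.

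The first option costs a one-sentence replacement in the Analysis section, a short clarification under Data collection, and the loss of one secondary comparison. It needs no new data.
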